### Study design and duration

This is a multi-centre, randomised, controlled surgical trial with internal pilot and embedded qualitative process evaluation, comparing immediate tonsillectomy versus conservative management (delayed surgery). The internal pilot will recruit patients over a 6-month period and, subsequent to successful completion, the main trial will commence and continue recruitment for a further 18 months.

The end of the study will be the date of the last participant’s 24-month follow-up visit and once all serious adverse events (SAEs) have been followed up.

Qualitative interviews for the qualitative process evaluation will be carried out on patients, staff and GPs during the internal pilot and at the end of the main trial.

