### Control

Participants in the control arm will receive conservative management and will be asked to defer surgery for up to 2 years. Conservative arm participants will receive the standard non-surgical care, as normally treated by the patients themselves or by the referring GPs in their current practice, which typically comprises self-administered analgesia plus/minus ad hoc primary care prescription of antibiotics, attendance at walk-in centres or A&E departments for more severe episodes. Participants will be reviewed at 12 months post randomisation and assessed on their willingness to remain in the delayed surgery arm.

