### Data collection and follow-up

All participants will be followed up for 24 months from the date of randomisation. Once consented, the participant will complete a baseline questionnaire booklet to be returned to NCTU. The participating site will then randomise the participant via the NCTU randomisation system. Participants randomised to immediate tonsillectomy will undergo surgery within 6–8 weeks of randomisation. All NATTINA participants will be prompted weekly by their preferred method of communication (short message service (SMS) message, Email or Interactive Voice Response (IVR) via telephone) to submit the number of sore throat days experienced in the previous 7 days, and requested to submit a STAR when they experience a sore throat. Through this the participant will provide details of the severity, use of any over-the-counter and prescription medications, the nature of any professional health care advice sought and the number of hours when unable to undertake usual activities (including work/studies). An additional SF-12 [26] will also be completed relative to the episode. The research nurse will contact participants randomised to the surgical arm at 1 and 2 weeks after their tonsillectomy to collect data concerning any adverse events. The participant will be asked to attend 2 further clinic visits and complete follow-up questionnaire booklets at 12 and 24 months, and to complete 2 other questionnaire booklets at home at 6-month and 18-month interim points. The 12-month clinic visit will allow participants in the conservative management group to be assessed on their willingness to remain in the deferred group. At their final 24-month visit these participants will be asked whether they wish to go forward for tonsillectomy. Adverse events and SAEs related to the study intervention will be collected throughout the duration of the study.

Consent will be sought to access participants’ GP health records in order to gather primary health care usage data at the end of their 24-month follow-up. Data collected will cover the participant’s 24-month follow-up and 12 months prior to randomisation, and will capture adverse events, number of contacts with primary and secondary health care services, prescribing information and other relevant material to support data retrieved from STARs and post-operative research nurse telephone calls (Table 1).

**Table 1 Tab1:** Data collection and time points

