### Study compliance and withdrawal

Where feasible, visit windows of ±6 weeks should ensure sufficient time is offered to facilitate scheduling appointments; non-attendance for study visits will prompt follow-up by telephone. Participants may also be contacted via telephone by the research nurse at the participating site to remind or encourage them to return questionnaires or weekly alerts. Source data verification will be performed by the Trial Manager at each participating site.

Participants will have the right to withdraw from the study at any time for any reason, and without giving a reason. The investigator will also have the right to withdraw participants from the study intervention if he/she judges this to be in their best interest. At the participants’ request, those in the conservative management arm will be able to cross over into the surgical arm or withdraw completely with no further data collected. Participants in the tonsillectomy arm will be able to either withdraw completely or cross over to the conservative management arm before surgery has occurred.

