### Economic analysis

‘Within trial’ economic analyses will be carried out from the perspective of the NHS. Costs will be based upon the costs of the randomised interventions received and on the use of subsequent care and services recorded on Case Report Forms and participant-completed questionnaires. Cost falling on participants and their families will also be recorded in a secondary analysis. Participant costs and time away from usual activities per each type of episode of care will be collected via questionnaire at 18 months. A micro costing exercise will be conducted to elicit the other resources required to estimate the costs of the surgical procedures. Other unit costs will come from nationally available data [28] and combined with use of service data to produce a cost for each trial participant. Discounting will be applied to costs and outcomes at UK recommended rates [29].Cost-effectiveness analysis – based on the incremental cost per sore throat day avoided.Cost-utility analysis – based on incremental cost per QALY gained. QALYs will be based upon responses to the SF-12 converted into SF-6D scores using standard algorithms. QALYs will be estimated from the responses from the SF-6D using the AUC method.For both the cost-effectiveness and cost-utility analyses the results will be presented as point estimates of mean incremental costs and effects as well as in stochastic analyses plots of cost and effects and cost-effectiveness acceptability curves.Cost-benefit analysis – a contingent valuation method to allow participants to state their preferences in monetary values [30], to avoid a sore throat day using a participant-completed questionnaire administered at baseline. For each randomised group we will calculate mean willingness to pay and explore how valuations might vary according to participant characteristics (e.g. family income, gender, age, etc.). The data on the willingness to pay for a sore throat day avoided will be combined with information on number of sore throat days experienced and on the cost per participants. The results will be presented as point estimates and in stochastic analysis plots of cost and mean willingness to pay and incremental net benefit curves.

For all economic evaluations deterministic sensitivity analyses will be performed to explore key uncertainties. Where appropriate these analyses will be combined with a stochastic analysis with the results presented in the same ways as described above.

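### The only economic horizon ends at 24 months, when controls are asked about deferred surgery, so operations accepted then carry no cost and postponed surgery looks like avoided surgery

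*Protocol article*

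**What the plan says.** All references are to the protocol article.

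- **Comparator.** Study design and duration describes the trial as "comparing immediate tonsillectomy versus conservative management (delayed surgery"). The Control section adds: "Participants in the control arm will receive conservative management and will be asked to defer surgery for up to 2 years". The Background explains that patients find deferral more acceptable than having no surgery.
- **Timing of surgery.** Under Data collection and follow-up, "Participants randomised to immediate tonsillectomy will undergo surgery within 6–8 weeks of randomisation". For controls, "At their final 24-month visit these participants will be asked whether they wish to go forward for tonsillectomy". Their willingness to stay in the deferred group is also reviewed at 12 months. Study compliance and withdrawal allows earlier switching: on request, "those in the conservative management arm will be able to cross over into the surgical arm or withdraw completely with no further data collected".
- **End of observation.** "All participants will be followed up for 24 months from the date of randomisation". Table 1 places the last questionnaires, the last case report form and the GP linkage at 24 months.
- **Economics.** The analyses are labelled within-trial and take the NHS viewpoint, with participant costs in a secondary analysis. On what is counted, the section says: "Costs will be based upon the costs of the randomised interventions received and on the use of subsequent care and services recorded on Case Report" (that is, the trial's own data forms), plus what participants report by questionnaire. The secondary objectives set a 24-month period for cost per sore throat day avoided and for cost per QALY, and Economic outcome measures repeats it for the former. Deterministic sensitivity analyses are promised, but the horizon is not named among the uncertainties they will cover.

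**The concern.** Any trial-based economic evaluation stops somewhere. Here it stops at the visit where the deferral period ends and controls are asked for their decision. A control who accepts surgery that day and one who no longer wants it look identical in the costing: both have zero tonsillectomy cost. The immediate arm's operations, at 6–8 weeks, lie wholly inside the window.

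This matters because of the intended use. The abstract's Discussion looks to NHS savings from avoiding unnecessary operations, and the Background wants modelled costs and consequences to inform the threshold for surgery. Both uses require avoided operations to be separated from postponed ones. The Statistical analysis section expects some controls to switch to surgery during follow-up, so some remaining demand at 24 months is plausible.

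**Working it through.** The article gives no figure for this point: no unit cost, no cross-over share and no uptake at 24 months. The check is an accounting identity with assumed inputs.

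**Step 1: which operations are counted.**
- Immediate arm, 6–8 weeks: inside the window and costed.
- Control crossing over before 24 months: an intervention received, so costed.
- Control accepting at the 24-month visit: done after the last data collection, so not costed. Recovery and complications are not observed either.

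**Step 2: notation.**
- C = cost of one tonsillectomy (unit of account)
- s = share of the immediate arm operated on
- x = share of controls crossing over before 24 months
- u = share of the remaining controls who have surgery following the 24-month visit
- r = annual discount rate

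**Step 3: formulas, per participant.**
- Net surgical cost within the trial: C(s − x)
- With deferred operations counted: C[s − x − (1 − x)u/(1 + r)²]
- Amount left out: C(1 − x)u/(1 + r)²

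**Step 4: numbers.** Assumed s = 1 and x = 20%, so the within-trial figure is 1 − 0.20 = 0.80 C. The article says UK recommended discount rates will be used but gives no value; 3.5% is an assumption, with (1.035)² = 1.071. Six hundred participants at 1:1 gives 300 controls, so uncounted operations = 300 × 0.80 × u.

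| u | Left out, r = 0 | Net cost, r = 0 | Within-trial ÷ net | Net cost, r = 3.5% | Uncounted operations per 300 controls |
|---|---|---|---|---|---|
| 10% | 0.08 C | 0.72 C | 1.11 | 0.73 C | 24 |
| 25% | 0.20 C | 0.60 C | 1.33 | 0.61 C | 60 |
| 50% | 0.40 C | 0.40 C | 2.0 | 0.43 C | 120 |
| 75% | 0.60 C | 0.20 C | 4.0 | 0.24 C | 180 |

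With s = 1 and no discounting, the ratio is (1 − x)/[(1 − x)(1 − u)] = 1/(1 − u), so it does not depend on x. With s = 0.9 and x = 20%, the within-trial figure is 0.70 C, against 0.62, 0.50, 0.30 and 0.10 C undiscounted.

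**Step 5: what the table does not show.** The ratio grows quickly because its denominator shrinks, so the amount left out is the steadier measure. The ratio covers surgical cost only. GP, prescription and A&E costs also enter incremental cost, so it is not the ratio for total incremental cost, nor for cost per QALY or per sore throat day.

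**The case against.** Four points can be made in defence of the plan.

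1. *The horizon cuts off effects as well as costs.* It drops any continued relief in the immediate arm and any later relief in controls operated on after month 24. This stands. A reader might infer that cost per QALY and cost per sore throat day avoided are overstated, but the document gives no post-24-month effects, so the net direction for those ratios is not established.

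2. *Not all deferred operations are missing.* Controls may switch at any time, and those operations are costed. This also stands: only surgery taken up at or after the final visit is left out.

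3. *The 24-month comparison answers the stated objective.* The primary objective compares the two policies over 24 months, the horizon is openly stated, and the Control section describes ordinary non-surgical care. The base case is therefore valid for the first two years, and nothing is concealed. But the design section itself calls the comparator delayed surgery, and two-year costs alone cannot show how much of the control arm's lower surgical cost is postponement.

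4. *Scenario lists belong in a fuller plan.* An unseen health economics plan may cover this, and the article promises sensitivity analyses and modelling of pathways. However, the article does fix a within-trial horizon of 24 months alongside a delayed-surgery comparator, and ties none of that modelling to a longer period.

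A scenario that added only late costs would also be lopsided. The imbalance is smaller than it seems for controls operated on at about month 24, since they and their immediate-arm counterparts are both post-tonsillectomy from then on and later benefit largely cancels. That is an assumption to be stated and varied.

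**Conclusion.** The point holds for incremental surgical cost. As a measure of immediate versus deferred tonsillectomy, the within-trial figure is too high by C(1 − x)u, discounted, per participant. With x assumed at 20%, this is 0.08 C to 0.60 C undiscounted for uptake of 10% to 75%. Those uptake values are illustrative. High ones would mean that most controls who went two years without surgery then choose it, and the document offers no basis for picking a value.

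Two stronger readings are not supported: that the bias in cost per QALY or per sore throat day has a known direction, and that the 24-month analysis is invalid. The weakness is that 24 months is the only horizon fixed, and it ends where the deferral ends. The primary clinical outcome is not affected.

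**What to change.** 1. Keep the 24-month base case, and state in Economic analysis that it does not cover surgery taken up at or after 24 months.
2. Record each control's answer at the 24-month visit as a data item.
3. Name in Economic analysis one deterministic scenario, reported beside the base case. It adds the discounted tonsillectomy cost from the planned micro-costing, and the post-operative loss seen in participants operated on during the trial, for controls opting for surgery.
4. Run it over a range of actual uptake, because stated intention may exceed it. State the assumption about benefit after 24 months in both arms, and vary it.

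The cost is one extra scenario. The question is already asked, and the micro-costing and sensitivity analyses are already planned, so no further visit is needed. The scenario relies on stated intention and on an assumption about later effects, and should be labelled accordingly. The data item has to be in place before the first 24-month visits.

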### Qualitative process evaluation

A selection of recruited and declining patients, staff and GPs will be invited to participate in a qualitative interview to discuss their expectations, motivations for participation and their views and experiences of sore throat and of the NATTINA trial. Recruited participants who signed a consent form allowing a researcher from Newcastle University to approach them to discuss an interview will be contacted during the internal pilot or towards the end of the main trial and invited for an interview. Patients who decline to participate in the main trial will be offered an expression of interest form that they can complete and return to NCTU. A researcher will then contact the patient and arrange an interview at a time and location convenient for them. Written informed consent will be obtained at the beginning of the interview.

### Data handling and record keeping

Data will be recorded by authorised staff and stored in a secure web-based electronic data capture system (MACRO) designed and maintained by NCTU hosted on secure servers at Newcastle University. The validated database will have restricted and limited access and data transferred from site by remote access will be encrypted. Analysis of this data will be undertaken by NCTU staff. Subjects will be identified by a unique study number allocated by the randomisation system, which will be used on CRFs and questionnaire front covers. Personal details (full name, address, phone numbers, Email address and NHS number) as well as their preferred method of communication (SMS, Email, telephone) will be collected by the research nurse once the participant has been recruited, and the form faxed to NCTU via SOHO 66 (secure fax to Email system) where it will be used to send out follow-up questionnaires to participants. Selected personal information will be inserted into a database managed by an independent technology solutions company for the sole purpose of distributing weekly sore throat alert prompts and STARs centrally. Databases containing identifiable information will be secure and password protected.

All interviews for the qualitative process evaluation will be audio-recorded and transcribed verbatim. Audio files and anonymised transcripts will be securely stored in password protected files.

Data will be handled, computerised and stored in accordance with the Data Protection Act 1998. Caldicott approval will be sought during set-up at each participating site to enable the collection and transfer of participant information as part of this study. All study data will be archived for 5 years and in accordance with GCP and NCTU SOP.

### Study compliance and withdrawal

Where feasible, visit windows of ±6 weeks should ensure sufficient time is offered to facilitate scheduling appointments; non-attendance for study visits will prompt follow-up by telephone. Participants may also be contacted via telephone by the research nurse at the participating site to remind or encourage them to return questionnaires or weekly alerts. Source data verification will be performed by the Trial Manager at each participating site.

Participants will have the right to withdraw from the study at any time for any reason, and without giving a reason. The investigator will also have the right to withdraw participants from the study intervention if he/she judges this to be in their best interest. At the participants’ request, those in the conservative management arm will be able to cross over into the surgical arm or withdraw completely with no further data collected. Participants in the tonsillectomy arm will be able to either withdraw completely or cross over to the conservative management arm before surgery has occurred.

### Statistical analysis

The primary outcome measure of the total number of sore throat days reported over the 24 months of follow-up will be analysed using negative binomial regression in order to compare any change between the NATTINA arms while adjusting for the stratification variables used – recruiting centre (as a random effect) and baseline severity (as a fixed effect). This analysis will be undertaken on an intention-to-treat basis; however, participants may switch over from conservative to surgical management. In the NATTINA design, although participants are asked to commit to ‘deferred surgery’, we anticipate that a number of participants will take up the opportunity to switch to surgery. The implication of such cross over, which typifies surgical trials, is that the intention-to-treat analysis will produce a very conservative estimate of the effect of tonsillectomy. We will, therefore, undertake a planned ‘as treated’ analysis with repeated measures corresponding to two periods of follow-up for those participants who cross over from medical management to tonsillectomy. The length of these follow-up periods will act as an exposure variable in the negative binomial regression.

QOL scores based on the SF-12 will be calculated according to the scoring manual at baseline and 6, 12, 18 and 24 months post randomisation. The scores will be analysed using models developed for longitudinal data. The dependent variable will be the QOL score for an individual patient at a particular occasion. Both variation between patients and variation between occasions nested within patients will be modelled as random effects with a normal distribution. Differences between groups and changes over time will be modelled as fixed effects. The analysis will be adjusted for the differences between strata.

The analysis of other secondary outcomes will follow a broadly similar strategy; repeated measures will be analysed using a random effects model with an appropriate error structure. Should data be found to be non-normally distributed, the use of transformations or non-parametric approaches will be considered.

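### As worded, the SF-12 model places the pre-randomisation score among the responses and names no baseline covariate, group-by-time term or reported contrast

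*Protocol article*

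**What the plan says.** The Statistical analysis section of the protocol article describes the SF-12 model piece by piece.

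- Occasions: the scores "will be calculated according to the scoring manual at baseline and 6, 12, 18 and 24 months post randomisation".
- Approach: "The scores will be analysed using models developed for longitudinal data".
- Response: "The dependent variable will be the QOL score for an individual patient at a particular occasion". Baseline is not excepted.
- Random part: "Both variation between patients and variation between occasions nested within patients will be modelled as random effects with a normal distribution". This amounts to a random intercept with equal correlation between any two occasions.
- Fixed part: "Differences between groups and changes over time will be modelled as fixed effects".
- Adjustment: "The analysis will be adjusted for the differences between strata". The Randomisation section gives the strata as centre and severity.

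For the remaining secondary outcomes, "The analysis of other secondary outcomes will follow a broadly similar strategy". Table 1 shows TOI 14 collected at the same five scheduled times as the SF-12. The Data collection and follow-up section has the baseline booklet completed after consent and before the site randomises.

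**The concern.** Randomisation makes the expected difference between arms at baseline zero. If the baseline score is one of five response rows and a single group coefficient is fitted across all five, that coefficient averages four occasions that can carry a treatment effect with one that cannot. The estimate is then pulled towards no difference.

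The baseline score is also the obvious covariate for the later scores, and the text does not use it as one. Adjusting for centre and a severity stratum is not the same as adjusting for the participant's own baseline SF-12 score.

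At stake is the trial's quality-of-life comparison, which is a named secondary objective, and possibly TOI 14. The same section already expects cross-over to make the intention-to-treat estimate conservative. Dilution from a pre-randomisation visit would add attenuation that is easy to avoid.

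**Working it through.** **Plan's own figures.** The article gives no effect size, power or precision for the SF-12. Its 224 per arm belongs to the primary outcome. It reproduces with a difference of 3.6, SD 10.8, 90% power and two-sided 2.5% (n = 224, power 0.901), and 448/0.75 = 597.3, rounded up to 598, agrees with 600. It is used below only as a sample size.

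**Inputs.** From the article: five occasions, one before and four after randomisation; patient and occasion-within-patient random effects; 25% loss over 24 months. Assumed: unit variance and within-person correlation r of 0.5 to 0.7 (0.3 to 0.7 where stated).

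**Step 1: dilution under the additive reading.** With complete data and equal correlation, the group coefficient is the difference between arms in five-occasion means:

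(0 + D6 + D12 + D18 + D24)/5 = 0.8 × the average follow-up effect.

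For a constant effect D this is 4D/5 = 0.80D, whatever r is.

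**Step 2: dropout.** Baseline is then the best-observed occasion and gains weight. Spread the 25% loss evenly over the four visits (assumption), so that 93.75%, 87.5%, 81.25% and 75% are observed. The expected generalised least squares coefficient is 0.75D, 0.74D and 0.73D at r = 0.3, 0.5 and 0.7, a shrinkage of about 25 to 27%.

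**Step 3: cost in sample-size terms (complete data).** The required n is proportional to variance divided by the squared expected estimate.

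- A, additive model with baseline as a response: [(1+4r)/5]/0.64
- B, mean of the four follow-up visits, no baseline adjustment: (1+3r)/4
- C, mean of the four follow-up visits, baseline score as covariate: (1+3r)/4 − r²

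| r | A | B | C | A/B: dilution alone | A/C: dilution plus lost adjustment |
|---|---|---|---|---|---|
| 0.5 | 0.9375 | 0.625 | 0.375 | 1.50 | 2.50 |
| 0.6 | 1.0625 | 0.700 | 0.340 | 1.52 | 3.12 |
| 0.7 | 1.1875 | 0.775 | 0.285 | 1.53 | 4.17 |

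**Step 4: the group-by-time reading.** With separate arm means at every occasion, including baseline, the follow-up contrast is undiluted. Its cost against C depends on which contrast is reported:

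- Plain follow-up difference, B/C: 0.625/0.375 = 1.67; 0.700/0.340 = 2.06; 0.775/0.285 = 2.72 at r = 0.5, 0.6, 0.7.
- Difference in change from baseline, with variance (1+3r)/4 + 1 − 2r: 0.625/0.375 = 1.67; 0.500/0.340 = 1.47; 0.375/0.285 = 1.32.

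**Step 5: illustration.** Take 224 per arm, two-sided 5% and a true effect of 0.2 SD (the last two assumed). At r = 0.3, 0.5 and 0.7, power is 72%, 59% and 49% for A; 87%, 76% and 67% for B; and 93%, 93% and 98% for C.

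**The case against.** A reader might infer that the SF-12 effect will be shrunk by 20%. The documents do not support that. The fixed-effects sentence is a one-line description and not a closed list of terms. It does not exclude a group-by-time term, and nothing says that the reported result is the group main effect pooled over five occasions. With group-by-time contrasts the dilution is nil. The sentence naming baseline is also about scoring, and baseline would be scored under any plan. This stands: the shrinkage is conditional.

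A reader might also take the 2.5 to 4.2-fold figure as the size of a bias. It is not. Only about 1.5-fold is dilution; the rest is the gain from adjusting for the baseline score. The correlations are assumed, and the planned adjustment for strata, which include baseline severity, would recover part of that gain.

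For TOI 14 the article promises only a broadly similar approach with a suitable error structure. To say that its estimates would be biased goes further than the text.

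Two other defences carry less weight. The first is that the detail belongs in the statistical analysis plan, which the article says will govern the analysis. That answers an omission, but here the article does state the occasions, response, random effects, fixed effects and adjustment. A plan that follows this wording literally inherits the weakness. The second is the planned secondary analysis adjusted for clinical and demographic variables. It does not name the baseline SF-12 score, and adding such covariates would not take the baseline row out of the response.

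**Conclusion.** The point holds in conditional form. On its plain reading the SF-12 model has a pre-randomisation row among the responses, no baseline-score covariate and no stated contrast.

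- If the additive group effect is reported, the estimate is 0.8 of the average follow-up effect with complete data. It is about 0.73 to 0.75 of a constant effect under evenly spread 25% dropout.
- If group-by-time contrasts with unconstrained baseline means are reported, there is no dilution, but precision is still lost (about 1.3 to 2.7-fold in sample-size terms for r of 0.5 to 0.7, depending on the contrast).

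These figures assume equal correlation and equal variance across occasions. The sample-size ratios also assume complete data and make no allowance for strata. Under either reading the wording gives up something that a baseline score already collected would supply. The matter deserves correction but is confined to secondary outcomes: the primary negative binomial analysis does not use this model, nor do the area-under-the-curve QALYs.

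**What to change.** Replace the fixed-effects sentence with one that states how baseline enters and what is reported. For example: the SF-12 scores at 6, 12, 18 and 24 months will be the responses, with baseline score, visit, arm, arm-by-visit and the stratification factors in the model; the arm difference will be reported at 24 months and averaged over follow-up.

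An equivalent choice is to keep baseline as a response and constrain the arms to a common mean there. That version also keeps participants whose baseline score is missing. Apply the same wording to TOI 14 if it is to follow this model.

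The cost is one sentence, carried through to the statistical analysis plan before any outcome data are analysed. No new data are needed, because Table 1 already schedules both instruments at baseline.
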